## Abstract

**Background:**

For patients with complex health and social needs, care coordination is crucial for improving their access to care, clinical outcomes, care experiences, and controlling their healthcare costs. However, evidence is inconsistent regarding the core elements of care coordination interventions, and lack of standardized processes for assessing patients’ needs has made it challenging for providers to optimize care coordination based on patient needs and preferences. Further, ensuring providers have reliable and timely means of communicating about care plans, patients’ full spectrum of needs, and transitions in care is important for overcoming potential care fragmentation. In the Veterans Health Administration (VA), several initiatives are underway to implement care coordination processes and services. In this paper, we describe our study underway in the VA aimed at building evidence for designing and implementing care coordination practices that enhance care integration and improve health and care outcomes for Veterans with complex care needs.

**Methods:**

In a prospective observational multiple methods study, for Aim 1 we will use existing data to identify Veterans with complex care needs who have and have not received care coordination services. We will examine the relationship between receipt of care coordination services and their health outcomes. In Aim 2, we will adapt the Patient Perceptions of Integrated Veteran Care questionnaire to survey a sample of Veterans about their experiences regarding coordination, integration, and the extent to which their care needs are being met. For Aim 3, we will interview providers and care teams about their perceptions of the innovation attributes of current care coordination needs assessment tools and processes, including their improvement over other approaches (relative advantage), fit with current practices (compatibility and innovation fit), complexity, and ability to visualize how the steps proceed to impact the right care at the right time (observability). The provider interviews will inform design and deployment of a widescale provider survey.

**Discussion:**

Taken together, our study will inform development of an enhanced care coordination intervention that seeks to improve care and outcomes for Veterans with complex care needs.

## Introduction

Care coordination has proved essential for improving patients’ access to care (1), clinical outcomes (2–4), and experiences of care (3, 5–7), as well as increasing provider satisfaction (8) and decreasing or controlling healthcare costs (7, 8), including among Veterans receiving care from the US Department of Veterans Affairs (VA) health care facilities (5, 7, 9). Although evidence to date is inconsistent regarding the design and effectiveness of tools to assess care coordination needs (10–12), care coordination appears to be most successful for patients with conditions that increase their risk for hospitalization, mortality and higher costs (3, 9, 13, 14). Such high-risk, high need populations are not limited to those with a specific set of comorbidities and may include people with health-related social needs (15, 16). Care coordination for people with complex care needs is multidimensional and spans a continuum of care (17–19). It encompasses reliable and valid patient assessment; effective communication between patient, caregiver, and providers; and linkages between the family, community, and healthcare system (17, 20). Integration across domains of care is needed, rather than separate care coordination layers (21).

In the VA, evidence on care coordination for patients with complex care needs has been emerging. In the randomized trial of enhanced care coordination services within the VA Patient Aligned Care Team (PACT) Intensive Management (PIM) model, adding care coordination to the established and effective PACT model (1, 7, 22, 23) increased patients’ primary care and social work services, and outpatient healthcare costs. The intervention was also associated with decreased inpatient costs, resulting in similar total costs of care (7) and modest improvements in patient experiences of care (5). Bauer and colleagues demonstrated in a randomized stepped-wedge implementation trial that incorporating a facilitator into the mental health team led to decreased mental health hospitalizations for patients with serious mental illness, and for those with more complex conditions, improved mental health component scores as well (9). Attention to the unique and complex needs of women Veterans also highlights the potential for care coordination to improve pregnancy and birth outcomes (24–26), and Medicare patients have benefited from care coordination after hospitalization through reduced mortality and healthcare costs (27). Receiving care in an integrated care setting like the VA when there are multiple providers might appear to be fragmented. However, integrated care with multiple providers may minimize hospitalizations for ambulatory care sensitive conditions, and enhance access to more timely or specialized care (28).

Despite this evidence, the extent to which care coordination is contributing to outcomes is not fully known. The core elements of care coordination interventions for patients with complex care needs have varied considerably across interventions and patient populations (20, 21). Core elements of care coordination interventions as described in a 2018 VA State of the Art Conference on Care include the contextual factors, locus (setting, level, and purpose), and design features (mechanisms and types of coordination such as structural, functional, normative, interpersonal, and clinical) and are essential in the design and evaluation of care coordination interventions (29, 30). In practice, lack of standardized needs assessment tools and processes has made it challenging for healthcare providers to determine the optimal amount and type of care coordination services based on patient needs and preferences (31), and thus to measure the dose-response relationship. Ideally, care coordination ensures that accountable structures and processes are in place for communication and integration of a comprehensive care plan across providers and settings that is aligned with patient and family needs, preferences, and goals (32). Further, ensuring that engaged care providers have reliable and timely means of communication about care plans is essential to inform provider actions and to overcome the potential for care fragmentation. A key challenge in delivering integrated patient care is to optimally balance coordination and patient centeredness.

The purpose of this paper is to outline what is known and not known about care coordination and its impacts among Veterans and describe our study underway in the VA. We will conduct a prospective observational multiple methods study, which will gauge the relationship between care coordination services and subsequent healthcare use among Veterans with complex care needs, assess Veterans’ perspectives about care integration in the services they have received, and assess provider perspectives about care integration and care coordination tools and processes. We describe potential limitations to our approach as well. Finally, we highlight how our approach may inform evidence building in other health care systems that can inform implementation of an improved care model that incorporates these perspectives, addresses the identified needs, and focuses care on aspects with the greatest potential to improve patient outcomes.

### Theoretical framework and logic model

In our prior work, we explored the linkages between care coordination theory and practice and considered three specific domains—the context surrounding an intervention, an intervention’s locus (setting, level, and purpose), and elements of its design (mechanisms and types of interventions) (29, 30). The linkages from theory to practice underpin measurement development and testing, which is important for evaluating care coordination processes and intermediate outcomes, and patient experiences of care coordination interventions.

To operationalize and develop measures to examine how care coordination relates to patient outcomes, we viewed care coordination as a process with a sequence of steps and corresponding outcomes to be measured. Figure 1 depicts components in a graphical chain of logic with a diamond box for care coordination tools and processes for assessing patient needs, arrows for the process flow, dotted lines for associations, rounded boxes for intermediate outcomes, rectangles for health states, and ovals for harms. In this case, the process starts at the point of assessing a person's needs and risks and posits the cause-and-effect relationships from that point onward that may result in favorable or unfavorable systems-level and patient-level outcomes, and informs key questions, such as:
1.At a population level (and without intervention), what are the predicted outcomes for each risk group as determined by a care coordination needs assessment?2.What is the effect of a needs-assessment-determined risk group intervention (assigned care coordination resources) on outcomes (e.g., morbidity, mortality, health care use and costs).3.In the absence of intervention, what proportion of patients are categorized into the “wrong” risk group (and proceed to have outcomes at different levels/rates than expected)?4.What are the associations between care coordination services and receiving the “right care at the right time”?5.Even with care coordination services, what proportion of patients do not receive any care or optimal care (“suboptimal/wrong care”)?6.What is the effect of “right care at the right time” on outcomes (e.g., morbidity, mortality, health care use and costs)?

**Figure 1 F1:**
[figure not shown]
Logic model: operationalizing care coordination process & outcomes.

### Study aims

With this guiding logic model, our multiple methods study comprises three aims intended to begin to address some but not all aspects. For Aim 1, we will focus on components 1–3 in the logic model by characterizing and comparing relationships between care coordination processes and health and care outcomes among Veterans with complex care needs. We will begin to address components 4 and 5 by surveying Veterans about their experiences regarding care coordination and the extent to which their needs were met (Aim 2). We will also interview and survey providers (Aim 3) about their perceptions of the attributes of care coordination needs assessment tools and processes that VA sites have implemented, including their improvement over other approaches (relative advantage), their fit with current practices at their facility (compatibility and innovation-fit), complexity, and the ability to visualize how the steps proceed to impact the right care at the right time (observability). To assess the extent to which the right care happens at the right time to potentially impact outcomes (component 6), we will combine information gathered from all three aims to describe scenarios that will exemplify the need for a future implementation study. Taken together our approach will inform development of enhanced care coordination processes with a goal of improving care integration and patient outcomes.

## Methods and analysis

As a multiple methods study, we have three aims, each with specific research questions, hypotheses, and design aspects. The design and methods for each study aim follows.

### Aim 1: relationships between process and outcomes

#### Research questions and hypotheses

In aim 1 our main research question is “Are care coordination services associated with differences in health and care outcomes, including emergency department (ED) and urgent care (UC) visits, hospitalizations, mortality, and healthcare costs among Veterans with complex care needs?” We hypothesize that receipt of care coordination services will be associated with fewer ED/UC visits and hospitalizations, decreased mortality, and reduced or neutral healthcare costs among these Veterans.

#### Objective and study sample

We will characterize and compare the relationship between receiving care coordination services and subsequent healthcare use, health outcomes, and healthcare costs among Veterans with high-risk, high-need conditions in a prospective observational study. With existing data available in the VA's electronic health record (EHR), VA-purchased care claims, and Medicare claims data from the Centers for Medicare and Medicaid Services (CMS), we will identify and match Veterans with complex care needs with and without care coordination services based on clinical and sociodemographic characteristics and prior healthcare use. The VA lacks a standardized care needs assessment in the EHR, but does include a means to identify Veterans with high risk for hospitalization and/or mortality, based on annual care assessment of needs (CAN) scores (33). Those with a CAN score of 85 or greater, indicating their predicted probability for hospitalization and/or mortality at one-year is at or above the 85th percentile, will be included. The CAN score is generated from VA EHR data and includes information on sociodemographic characteristics, chronic illness measures (including the Deyo-Charlson comorbidity index), VA healthcare use, vital sign parameters, laboratory test values, specific medication use, and 18 drug interactions. The CAN score has been well validated for predicting hospitalization and mortality and is in wide use in the VA. Use of the CAN score allows us to identify those most likely to benefit from care coordination and explore the relationships with processes and outcomes. Exclusion criteria include CAN score less than 85 and missing data for key variables required for matching. We will follow Veterans with complex care needs, with and without care coordination services over time to examine and compare their healthcare use, costs, and health outcomes.

To assess use of care coordination services, we will rely on information from VA documentation of service provision. In the VA, care coordination is documented as specific services in accordance with CMS coding and using Current Procedural Terminology (CPT) codes, including transitional care management, chronic care management and complex chronic care management codes and with detailed requirements for who can deliver the services and how frequently the services can be reported for CMS. VA care is not subject to the CMS frequency limits, however. Table 1 provides information on the CPT code categories and types of care coordination that will be used in our study.

**Table 1 T1:** CPT codes for care coordination services, description of services and allowed billing frequency based on Medicare requirements.

Code type	CPT code	Description	Providers who can deliver service	Allowed frequency of billing
TCM Codes	Code 99496	Transitional care management services with moderate medical decision complexity	Physician or non- physician practitioner such as PA, NP, CNS, and CNM	At post-hospital discharge; visit within 7 days of discharge
	Code 99495	Transitional care management services with high medical decision complexity		At post-hospital discharge; visit within 14 days of discharge
CCM	Code 99490	Chronic care management for a patient with multiple chronic conditions	Physician or non- physician practitioner such as PA, NP, CNS, and CNM, and their clinical staff such as RN, SW, and LPN	Once per calendar month; at least 20 min of time spent with patient per month
CCCM Codes	Code 99487	Complex chronic care management for a patient with multiple chronic conditions		Once per calendar month; 60 min of time spent with patient per month
CCM Codes	Code 99489	Each additional 30 min of time spent per month with patient on complex chronic care management services	Physician or non- physician practitioner such as PA, NP, CNS, and CNM	Once per calendar month
	Code G0506	Add on to initial CCM visit At time of in-person visit when providing care plan. Can be billed only once		At time of in- person visit when providing care Plan; can be billed only once
	Code T1016	Case management services		15-minute intervals; only used in VA, no longer used by CMS since 2013

Medicare Learning Network (34); Isetts et al. (35); Rivera et al. (36).

TCM, transition care management; CCM, chronic care management; CCCM, complex chronic care management; PA, physician assistant; NP, nurse practitioner; CNS, certified nurse specialist; CNM, certified nurse midwife; RN, registered nurse; SW, social worker; LPN, licensed practical nurse; VA, Veterans Affairs.

In planning this study, we queried the VA Corporate data warehouse to gauge the volume of care coordination workload in selected sites involved in the early phase of VA Care Coordination and Integrated Case Management initiative, which aimed to begin standardizing care coordination assessment across VA facilities (37). For Aim 1 we will include all VA facilities that offer care coordination services.

#### Outcome measures

Pilot data from FY2018 from one VA medical center were used to estimate a conservative sample size of cases (those with a needs assessment documented) and comparator patients for at least 12 VA facilities. We estimated a minimum of 88 cases per site; and with a 1:1 match for comparators, a total sample of 2,112. With growth in the number of VA sites expanding and documenting care coordination services, we expect this number to be easily surpassed during the observation period (FY2019–FY2021).

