#### Healthcare costs

We will estimate annual total healthcare costs (VA and Medicare), including outpatient, ED, UC, inpatient, and medication costs. For power calculation estimates, we rely on Yoon et al. (7), which indicates unadjusted VA costs for complex patients at $31,956 (95% CI $29,840, $34,443) in 2015 dollars. We estimated that we will have a minimum of 85.1% power to detect an effect size of 0.13–0.20 between Veterans with and without care coordination. We have considered the anticipated larger variance in costs expected as reported in prior research for cost estimations that include both VA and Medicare costs (1, 39, 40).

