#### Mortality

We considered experience of Wang et al. (33), and our own preliminary analysis of primary care patients with risk scores indicating high-risk, in which yearly mortality rates ranged from 6.2% to 7.9%. Using data from VA and CMS mortality sources (41), conservatively, using a 5% mortality rate among Veterans with care coordination, we have 81% power to detect a significant odds ratio (OR) of 1.6, with power increasing to 88% if the mortality rate among Veterans without care coordination is 8%.

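### Aim 1's stated mortality power does not follow from 2,112 Veterans matched 1:1 on the two-sided basis that reproduces its cost power, and the 1:1 ratio is not justified although comparators come from existing records

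*Protocol article*

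**What the plan says.** **Size and ratio.** Under Aim 1, Outcome measures, the protocol article projects from one medical centre's pilot data to cases and "comparator patients for at least 12 VA facilities". It then says: "We estimated a minimum of 88 cases per site; and with a 1:1 match for comparators, a total sample of 2,112". The paragraph describes this as a conservative estimate and adds: "we expect this number to be easily surpassed during the observation period (FY2019–FY2021".

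**Source of comparators.** Under Aim 1, Objective and study sample, with existing health-record, purchased-care and Medicare data, "we will identify and match Veterans with complex care needs with and without care coordination services". No recruitment is involved in Aim 1. The size of the eligible group without care coordination is not given.

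**Matching method.** The Aim 1 Analysis section leaves the approach open, with propensity score matching as an example, and names no ratio.

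**Stated powers.** Mortality: "using a 5% mortality rate among Veterans with care coordination, we have 81% power to detect a significant odds ratio (OR) of 1.6". The same section puts power at 88% for a comparator death rate of 8%. Healthcare costs: "minimum of 85.1% power to detect an effect size"; the effect sizes named run from 0.13 to 0.20. ED visits: 98.6%. Alpha of 0.05 appears only under Aim 2, Measures, and sidedness is not stated anywhere.

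**The concern.** There are two linked problems.

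1. The cost and mortality powers are presented for the same planned sample. If one reproduces on a standard basis and the other does not, at least one was calculated on an undeclared basis or is wrong. Decreased mortality is one of the Aim 1 hypotheses, and on the two-sided basis it is the least well powered of the three outcomes for which power is given.

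2. The limiting quantity in Aim 1 is the number of Veterans with documented care coordination. Comparators are drawn from records already held. A 1:1 ratio is natural when each control must be recruited; here it needs a reason, because a second or third comparator per case reduces the standard error without any new data collection.

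**Working it through.** **Inputs.** 12 sites × 88 cases = 1,056 cases; × 2 = 2,112, which reproduces the stated total exactly. Mortality with care coordination is 5%. The comparator rate is either 8%, or the rate implied by OR 1.6: 0.05 × 1.6 / (0.95 + 0.05 × 1.6) = 0.08/1.03 = 7.77%. Cost effect size d = 0.13 (lower end of the stated range). Alpha is 0.05, two-sided by assumption. Observations are treated as independent.

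**Step 1: find the basis from the cost figure.** Power = Φ(d/√(1/n₁ + 1/n₂) − z).
- Two-sided: 0.13/√(2/1056) = 2.987; 2.987 − 1.960 = 1.027; power 84.8%. The article states 85.1%.
- One-sided: 2.987 − 1.645 = 1.342; power 91.0%.

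The cost figure therefore fits two-sided 0.05 with 1,056 per group.

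**Step 2: mortality on the same basis.** Power = Φ((Δ − z·s₀)/s₁), where s₀ is the pooled (null) and s₁ the unpooled standard error.
- OR 1.6: Δ = 0.02767, s₀ = 0.010639, s₁ = 0.010622; (0.02767 − 1.960 × 0.010639)/0.010622 = 0.642; power 74.0%. Stated: 81%.
- 5% versus 8%: Δ = 0.03, s₀ = 0.010729, s₁ = 0.010709; (0.03 − 1.960 × 0.010729)/0.010709 = 0.838; power 79.9%. Stated: 88%.

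Unpooled, log-odds-ratio, arcsine, continuity-corrected and simulated Fisher exact versions stay, with the pooled one, at 71.0–74.4% and 77.3–80.4%. At 1:1 the stated powers need about 1,256 and 1,326 per group.

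**Step 3: one-sided 0.05.** Pooled: 83.1% and 87.6%. Log-odds-ratio: 82.6% and 87.0%. Continuity-corrected: 80.7% and 85.7%. This comes close to both stated figures but would put mortality on a different basis from cost.

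**Step 4: more comparators per case.** Same formulas, 1,056 cases, 1,056k comparators, two-sided. Relative to 1:1, the standard error of a mean difference with equal variances is √((1 + 1/k)/2).

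| Ratio | Relative SE | OR 1.6 | 5% vs 8% | Cost, d = 0.13 |
|---|---|---|---|---|
| 1:1 | 1.000 | 74.0% | 79.9% | 84.8% |
| 1:2 | 0.866 | 84.5% | 89.4% | 93.2% |
| 1:3 | 0.816 | 88.4% | 92.6% | 95.5% |
| 1:4 | 0.791 | 90.3% | 94.1% | 96.5% |

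The gains from 1:2 to 1:4 are 10.5–16.4, 9.5–14.2 and about 8–12 points. ED visits, stated at 98.6%, can gain at most 100 − 98.6 = 1.4 points. Most of the benefit comes from the second comparator.

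**Step 5: above the minimum case count.** Taking 88 cases per site and 1:1, two-sided, 15 sites (1,320 cases) give about 83% and 88% for mortality. With 29 sites (2,552 cases), OR 1.6 power is about 98% and cost power 99.6%, and going to 1:4 adds under 2 points to either.

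**The case against.** The best defence is that 2,112 is a floor. The article calls it conservative, intends to include every VA facility offering care coordination, expects to exceed the number, and counts 29 sites with active programmes under Aim 2. About three sites beyond the 12 would bring 1:1 matching to roughly both stated mortality powers, and at 29 sites the ratio hardly matters. This stands as a limit on the gain from extra comparators. It does not repair the mortality figures, because no larger sample is named for them and the cost power reproduces at 1,056 per group.

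Second, the mortality mismatch is a calculation question and was not caused by choosing 1:1; one-sided testing nearly explains it. That also stands, so the powers must be restated whatever ratio is used. A one-sided mortality test beside a two-sided cost test would still have to be declared.

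Third, 1:1 is a common trade of precision for closeness in an observational comparison, and matching on clinical and sociodemographic characteristics and prior use may leave few close candidates. This is fair, and the reason any higher ratio should be conditional on balance.

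A reader might infer more than the article supports: that the plan binds the analysis to 1:1 and discards the remaining comparators, that extra comparators cost nothing, or that they sit at the same facilities. The ratio appears only in the sample-size paragraph, the Analysis section fixes none, and neither pool size nor a same-facility rule is given.

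**Conclusion.** The point holds in two parts. First, at the stated minimum of 2,112 matched 1:1, two-sided mortality power is about 74% and 80%, which is 7 to 8 points below the stated 81% and 88%. Two-sidedness is my assumption; it rests on the cost figure, which reproduces only that way. Second, the only ratio given is unexplained, and at the minimum case count 1:2 matching alone would exceed both stated mortality powers (84.5% and 89.4%).

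A loss of some 11 to 16 points should not be read as the price of 1:1 across Aim 1. That range belongs to the OR 1.6 scenario, two-sided, at exactly 1,056 cases. It is smaller for the other outcomes and, at 29 sites with 88 cases each, under 2 points for mortality or cost. The calculations assume independent observations; site clustering or covariate adjustment could lower power further. They also assume enough eligible comparators, which the article does not establish.

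**What to change.** 1. State the sidedness and alpha for each Aim 1 outcome, and restate the mortality powers for 2,112 at 1:1 (about 74% and 80% if two-sided). If the stated figures came from a one-sided test or a larger sample, say so and reconcile them with the cost power.

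2. Report the number of eligible Veterans without care coordination. Then allow variable-ratio matching of up to four comparators per case where the pool and balance permit, with the same matching variables and the same caliper for every comparator, and weights for the ratio. Step the ratio down if balance fails. If 1:1 is kept, give the reason.

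3. Restate the total sample and the powers for the chosen ratio: 3,168 Veterans at 1:2 (1,056 × 3) or 5,280 at 1:4 (1,056 × 5) at the minimum case count.

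The cost is revised wording and a little more programming, with no recruitment. The downside is that third and fourth matches will be slightly less close, which the common caliper and balance checks limit.
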